### Ethical considerations

This study was reviewed by the Institutional Review Board of Kongju National University (KNU-IRB-2022-010) and adhered to the Declaration of Helsinki. Women who want to participate in the study will complete and sign a written informed consent form.

### Statistical analysis

This study will use SPSS for Windows version 24.0 (IBM Corp., Armonk, NY, USA). The t-test and chi-square test will be used for homogeneity testing between the two groups. To test normality, linearity, and residual independence, the Shapiro-Wilk test will be used for the primary and secondary outcome variables. If the homogeneity test shows statistically non-significant differences between the two groups, the independent t-test will be used to compare the outcome variables between the groups. If the homogeneity test yields a statistically significant difference for even one independent variable, Analysis of covariance (ANCOVA) as a general linear model will be used to adjust the confounding variables. ANCOVA will test the following hypothesis: The intervention group would have higher scores for environmental health perceptions, behavior, psychological status, and quality of life after the DECO-MOM intervention than the control group.

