### Sample size

The sample size was calculated using G*Power 3.1.0 [32] with the following specifications: a one-tailed test; the independent-sample t-test; power, 0.70; effect size (f), 0.53; significance level of the one-sided test, 0.05; and a 1:1 allocation ratio [17]. The effect size (Cohen’s d) for the difference between the intervention and control group in primary outcomes was calculated based on a previous study [17]. The score for individual environmental behavior was 58.59 ± 12.25 in the intervention group and 51.93 ± 12.64 in the control group, resulting in a Cohen’s d of 0.53 [Cohen’s d = (51.93–58.59) ⁄12.446528 = 0.53]. The resulting sample size was determined to be 35 in each group. Even though the drop-out rate in the previous study was 5.8% (with a final total of 96 subjects out of 102 enrollments) [17], this study will adopt a more conservative rate of 10%. In conclusion, 40 subjects will be recruited for each group.

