A strength of this study will be that it analyzes the effectiveness of the intervention on secondary outcomes that reflect psychological aspects. An antecedent systematic review and meta-analysis of prenatal education using internet-based interventions was able to draw inferences regarding depression, anxiety, quality of life, and satisfaction [36]. Environmental pollution and environmental health factors, such as fine particulate matter, air pollution, heavy metals, and chemicals have been linked to depression, anxiety, and stress in the general population [37] and in pregnant women [38]. A web-based intervention was found to be more effective on depression and psychological well-being than a home-based intervention [39]. In previous studies, an internet-based intervention alleviated depression, but more validation was needed in the other psychological aspects, including anxiety [36]. Satisfaction was also affected by internet-based prenatal education [40]; hence, the secondary outcome variables were set in an evidence-based manner.

Another strength of this study will be that it minimizes confounding factors by conducting analysis of covariance using ANCOVA. This study will have a risk of bias from controlling the confounding variables of the educational effect. In order to offset this bias, appropriate statistical methods will be needed in the analysis process. Accounting for selection bias through homogeneity testing and covariate analysis will be required for participants’ characteristics observed before the start of education [41]. In the quality appraisal, intervention type, recruitment location, and the frequency, intensity, and timing of interventions should be clear and explicit at the protocol stage prior to the initiation of education [41]. Therefore, the educator should check that the intervention is implemented as intended, and manage the intervention so that the dropout rate between the intervention groups is not imbalanced or the dropout rate is excessively high.

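### Baseline significance tests choose between an unadjusted t-test and ANCOVA, so chance picks the model and the pre-test score is usually left out

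*Protocol article*

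**What the plan says.** The Statistical analysis section of the protocol article first tests the two arms for baseline homogeneity by t-test and chi-square test, and then sets two branches:

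- "If the homogeneity test shows statistically non-significant differences between the two groups, the independent t-test will be used to compare the outcome variables" between the arms.
- "If the homogeneity test yields a statistically significant difference for even one independent variable, Analysis of covariance (ANCOVA) as a general linear model" is used, with the purpose of adjusting for confounders.

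No significance level is given for the homogeneity tests, and the covariates of the ANCOVA are not listed. The hypothesis concerns scores after the intervention, so the t-test branch compares post-test scores. Nothing makes the pre-test score a standing covariate, although Table 2 in the Assessments section schedules WEHP, WEHB, EPDS, GAD-7 and EQ-5D both before and after the intervention.

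The Sample size section is built on the unadjusted comparison: "a one-tailed test; the independent-sample t-test; power, 0.70; effect size (f), 0.53". The Discussion puts the analysis without its condition: "Another strength of this study will be that it minimizes confounding factors by conducting analysis of covariance using ANCOVA".

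**The concern.** If women are properly randomised, every baseline difference between the arms is due to chance. A significance test at baseline then cannot reveal confounding; it only decides at random which model is fitted. It also selects covariates by the wrong criterion: whether a variable happens to be imbalanced, not whether it predicts the outcome. The strongest predictor at hand is likely to be the pre-test score of the same scale, which the trial collects for both primary outcomes and mostly would not use.

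Two things are at stake. The trial gives up precision that its own pre-test would supply at no extra cost, in a design planned for only 70% power. And a pre-test imbalance that falls just short of significance stays in the unadjusted treatment estimate.

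**Working it through.** **Inputs.** From the Sample size section: "58.59 ± 12.25 in the intervention group and 51.93 ± 12.64 in the control group"; "significance level of the one-sided test, 0.05; and a 1:1 allocation ratio"; "The resulting sample size was determined to be 35 in each group"; and for dropout "this study will adopt a more conservative rate of 10" percent, giving 40 recruited per group. From the Assessments section: six baseline characteristics (age, gestational age, gravidity, parity, living child, medical history) and five pre-tested scales, 11 variables in all. The Other questions section names more. Assumed, because the article does not give them: a 0.05 level for each homogeneity test, and a pre-post correlation r of 0.3 to 0.7.

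**1. The plan's own figure.** d = (58.59 − 51.93)/12.446528 = 0.535, used as 0.53. An exact noncentral-t calculation at one-sided 0.05 gives 35 per group, with power 0.709. Then 35/0.90 = 38.9, so 39, against the stated 40. The sample-size arithmetic is not at issue. With 10% dropout, 40 × 0.90 = 36 per arm remain, and 36 is used below.

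**2. How often the ANCOVA branch is triggered.** For k independent tests, P(at least one significant) = 1 − 0.95^k:

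- k = 5: 23%
- k = 11: 43%
- k = 16: 56%

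Correlated variables lower this. With an assumed correlation of 0.5 among ten of the 11, it is about 33%.

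**3. How often the pre-test score is used.** If only significantly imbalanced variables enter the model, the pre-test score of a given outcome enters when its own test is significant, in about 5% of trials. If the ANCOVA branch always included it, it would still be unused in about 57% of trials at k = 11.

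**4. Power** (36 per arm, d = 0.53, one-sided 0.05, 11 independent baseline variables). The always-ANCOVA column is the noncentral-t value with residual SD √(1 − r²) and 2n − 3 degrees of freedom; the other two columns are simulated and are good to about 0.01.

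| r | Gated rule, only imbalanced variables enter | Gated rule, ANCOVA branch always includes pre-test | ANCOVA on pre-test in all cases |
|---|---|---|---|
| 0.3 | 0.71 | 0.72–0.73 | 0.75 |
| 0.5 | 0.71–0.72 | 0.75–0.76 | 0.82 |
| 0.6 | 0.71–0.72 | 0.77–0.78 | 0.87 |
| 0.7 | 0.71–0.72 | 0.80–0.81 | 0.93 |

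Simulated always-ANCOVA power agrees to about 0.01. At 35 per arm the gated rule gives 0.70 to 0.72. The unadjusted t-test alone has power 0.72 at 36 per arm.

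**5. Overall error and bias.** Over all randomisations, the simulated one-sided type I error of the gated rule is 0.04 to 0.05, on the low side when r is high. Its mean estimate is 0.53 when the true effect is 0.53.

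**6. An imbalance that escapes the gate.** A pre-test difference with t = 1.9 is not significant, so it does not trigger adjustment. It shifts the unadjusted estimate by r × 1.9 × √(2/36) = r × 0.448 SD:

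- r = 0.5: 0.22 SD, which is 0.22/0.53 = 42% of the planned effect
- r = 0.7: 0.31 SD, which is 59% of it

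The shift goes in whichever direction the imbalance happens to lie.

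**The case against.** The best defence is that the rule does no damage to what was promised. It is written in advance and depends on baseline data, not on outcomes. Type I error is held overall, the estimate is unbiased over randomisations, and the 0.70 power for which the trial was sized is met. All of that stands, and it limits the point to lost efficiency and an estimate left exposed to chance imbalance.

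Two further objections stand in part. The article does not define the ANCOVA covariates, so the sponsor may mean to include the pre-test score whenever ANCOVA is run; the power gap then shrinks to about half, but does not close. And the 43% rests on independent tests at an assumed level, which is why a range is given.

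A reader might infer more than this:

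- **That false positives are inflated.** For a pre-test imbalance of t = +1.9 favouring the intervention, the one-sided rate is 1 − Φ((1.645 − 1.9r)/√(1 − r²)), which is 21% to 33% at r = 0.5 to 0.7. For t = −1.9 the same formula gives about 0.1% or less. Over all randomisations the rate is 0.04 to 0.05.
- **That the analysis is chosen after results are seen.** What varies is the model selected by baseline data under a stated rule; this is not outcome-driven selection.
- **That ANCOVA would rarely be run.** It is the pre-test score that is rarely used.
- **That the Discussion contradicts the analysis section.** The same paragraph calls for homogeneity testing together with covariate analysis, so its sentence on ANCOVA is loose shorthand.

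That an analysis plan may exist does not remove the point. The article does not leave the choice open; it fixes it, and fixes it poorly.

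**Conclusion.** The point holds as one of efficiency and of a poorly chosen model rule. Chance decides whether ANCOVA is run (about 23% to 56% of trials for 5 to 16 independent tests at an assumed 0.05), and the pre-test score is left out in most trials on either reading of the ANCOVA branch. Compared with always adjusting for the pre-test, the gated rule gives up about 0.04 of power at a correlation of 0.3 and about 0.2 at 0.7; if the ANCOVA branch always carries the pre-test, the loss is about 0.02 to 0.12. It rests on sound randomisation, independent baseline variables and the assumed correlation range, which the article does not supply. The documents do not support a claim of inflated error or of a trial short of its planned power. It should be fixed, but the trial's validity does not depend on it.

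**What to change.** In the Statistical analysis section:

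- Delete the homogeneity gate.
- Analyse WEHP, WEHB, EPDS, GAD-7 and EQ-5D in all cases by ANCOVA of the post-test score on arm, with the pre-test score of the same scale and health centre as covariates. Centre belongs in the model because the Allocation section fixes 20 women per arm in each city.
- Report the adjusted mean difference. Take its confidence interval and the one-sided p-value from the arm coefficient, since the ANCOVA F-test has no direction.
- Compare e-learning satisfaction, which has no pre-test, between arms adjusted for centre only.
- Keep the unadjusted t-test as a sensitivity analysis, and show baseline characteristics descriptively.

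Align the Discussion sentence on ANCOVA with this. The t-test sample size can stay as a conservative basis.

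The cost is wording only. The pre-test is already scheduled, the Trial status section says recruitment has not started, and no extra participants or measurements are needed.

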## Discussion

This study will examine the effectiveness of a mobile application named DECO-MOM for pregnant women to enhance environmental health perceptions and behaviors as the primary outcome, and decrease depression and anxiety, increase quality of life, and e-learning satisfaction. The randomized controlled trial will enroll 80 subjects at two health care centers. This intervention will provide a valuable example of internet-based birth education for a vulnerable population to overcome the limitations of space and time [16]. As a mobile application, this program can be expanded to remote regions.

This intervention was carefully designed according to a theoretical basis. The primary outcomes of this study were derived from a theoretical framework according to the rPMT by Rogers [33]. Rogers argued that the concepts of reward and cost comprise an additional process for determining overall health behaviors, while severity, susceptibility, response efficacy, and self-efficacy are the main relevant concepts [33]. The inner cognitive mechanisms for determining environmental health behaviors, however, can be further examined in terms of the concept of cost. While severity and susceptibility may seem similar, severity refers to an individual’s perception of the harmfulness of health problems, whereas susceptibility refers to an individual’s perception of the likelihood that health problems will affect them [34]. Salazar [34] defined costs as the physical, social, and mental consequences of undertaking health behaviors. Therefore, it is necessary to emphasize environmental health issues from a macroscopic perspective and to present practical aspects of daily life and one’s own health to meet individuals’ needs from a microscopic perspective. The rPMT has been used in studies examining health information, accident prevention, political issues, and environmental issues [35], and it can be applied to modern environmental health issues and used in policies and studies that promote changes in environmental health behaviors for pregnant women.

A strength of this study will be that it analyzes the effectiveness of the intervention on secondary outcomes that reflect psychological aspects. An antecedent systematic review and meta-analysis of prenatal education using internet-based interventions was able to draw inferences regarding depression, anxiety, quality of life, and satisfaction [36]. Environmental pollution and environmental health factors, such as fine particulate matter, air pollution, heavy metals, and chemicals have been linked to depression, anxiety, and stress in the general population [37] and in pregnant women [38]. A web-based intervention was found to be more effective on depression and psychological well-being than a home-based intervention [39]. In previous studies, an internet-based intervention alleviated depression, but more validation was needed in the other psychological aspects, including anxiety [36]. Satisfaction was also affected by internet-based prenatal education [40]; hence, the secondary outcome variables were set in an evidence-based manner.

Another strength of this study will be that it minimizes confounding factors by conducting analysis of covariance using ANCOVA. This study will have a risk of bias from controlling the confounding variables of the educational effect. In order to offset this bias, appropriate statistical methods will be needed in the analysis process. Accounting for selection bias through homogeneity testing and covariate analysis will be required for participants’ characteristics observed before the start of education [41]. In the quality appraisal, intervention type, recruitment location, and the frequency, intensity, and timing of interventions should be clear and explicit at the protocol stage prior to the initiation of education [41]. Therefore, the educator should check that the intervention is implemented as intended, and manage the intervention so that the dropout rate between the intervention groups is not imbalanced or the dropout rate is excessively high.

This study will have several limitations. It will be a double-blinded randomized study; thus, the researchers will not be able contact pregnant women in person to provide social support given the need to guarantee anonymity. It is necessary to consider the risk of bias and report multiple effect estimates of the results [41]. The study population will be limited to participants capable of speaking and writing Korean in the light of cultural considerations, and to smart gadget owners; although smart gadget uptake is broad and nearly universal in Korea, economic exclusion will remain possible. Despite these limitations, this study will contribute to enhancing the environmental health conception and behaviors using a mobile application intervention, and it will serve as a valuable reference for future research.

### Trial status

The intervention is currently under development, and recruitment has not yet taken place.

## Data Availability

The data that support the findings of this study will be available from the corresponding author upon reasonable request.

## Abbreviations

ANCOVA: ANalysis of COVAriance
DECO-MOM: Deep ECOlogy-MOM
GAD-7: General Anxiety Disorder-7
e-LSS: e-Learning Satisfaction Scale
EPDS: Edinburgh Postpartum Depression Scale
EQ-5D: European Quality of life 5-Dimension
QR: Quick Response
rPMT: revised Protection Motivation Theory
TREND: Transparent Reporting of Evaluations with Nonrandomized Designs
WEHB: Women’s Environmental Health Behavior
WEHP: Women’s Environmental Health Perception
